# Efficacy and safety of a 4-step versus a 5-step egg ladder in children with IgE-mediated hen's egg protein allergy: protocol for an open-label randomized controlled trial

**DOI:** 10.3389/falgy.2025.1658186

**Published:** 2025-09-15

**Keywords:** paediatrics, food allergy, egg ladder, IgE-mediated hen's egg allergy, children

## Abstract

**Background:**

Introducing baked egg into the diet of children with hen's egg allergy (HEA) has been shown to potentially accelerate the development of tolerance to non-heated egg. However, there is no standardized egg ladder (EL) protocol, and different scientific societies across countries recommend varying versions. This study aims to assess the efficacy and safety of the four-step EL (4-EL) compared with the five-step EL (5-EL) in children with IgE-mediated HEA.

**Methods:**

We will perform an open-label randomized trial with two-parallel arms in two departments if the same academic hospital. A total of 84 children with IgE-mediated HEA will be allocated in 1:1 ratio to introduce hen's egg allergy into their diet according to either 4-EL or 5-EL with 4-week break period between subsequent steps. Oral food challenge (OFC) with tested products at each subsequent step of the EL will be conducted in hospital settings. The primary outcome will be the percentage of children with tolerance to non-heated hen's egg proteins defined as non-allergic reaction to raw hen's egg (0.5–1 egg, depending on the age of the patient) during the last OFC; measured at the end of the 18-week observation period for the 4-EL and 24-week observation period for the 5-EL. Secondary outcomes will include the percentage of children with negative OFC to each EL step; the percentage of children with anaphylaxis (including the percentage of those who were treated with epinephrine); the percentage of children with exacerbation of atopic dermatitis; growth; compliance; and quality of life of the caregivers and parents anxiety about adverse events during their child's OFC.

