### Study design

2.2

To compare both treatment strategies, we will conduct a multicenter, open-label, randomized superiority trial with two parallel arms and a 1:1 allocation ratio.

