### Sample size justification

2.9

This study is designed as a randomized controlled trial (RCT) to compare the clinical effectiveness and safety of two versions of an egg ladder protocol: one with four steps and the other with five steps, in children with IgE-mediated hen's egg allergy.

A formal sample size calculation based on statistical power was not feasible due to the lack of standardized data regarding allergen content and clinical reactivity across different baked egg preparations used in oral food challenges. As noted in the existing literature, studies assessing the immunological and clinical progression through the egg ladder remain limited, and standardized endpoints have not yet been universally defined.

Therefore, this trial was informed by available clinical evidence and precedent from similar studies involving the milk ladder in cow's milk-allergic children. In particular, a comparable RCT evaluating the impact of introducing baked cow's milk on tolerance development included 84 children (42 per arm) and demonstrated sufficient power to detect clinically meaningful differences (14).

Moreover, a recent randomized trial by De Vlieger et al. (12), which evaluated short- vs. long-term guided gradual egg reintroduction in baked egg–tolerant children, also enrolled 78 children (39 per arm) and successfully identified significant differences in tolerance acquisition timelines.

Based on this evidence and our clinical experience, a total of 94 children (47 per group) will be recruited to allow for an anticipated 10% dropout rate, ensuring that at least 84 participants (42 per group) complete the trial. This sample size is considered both feasible and appropriate to meet the study objectives while allowing an initial exploration of clinical differences between the two egg ladder variants. This pilot trial will generate effect size estimates to inform future confirmatory studies and formal sample size calculations.

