### Sequence generation and allocation concealment

2.16

Children will be randomised to either the intervention or control group immediately after enrolment. An independent investigator with no clinical involvement in the trial will generate random assignments using a computer-generated random number table. The random number will be generated in blocked randomization (using the block of 2) with a 1:1 allocation ratio. The randomization will be created using StatsDirect statistical software (Stats-Direct statistical software; http://www.statsdirect.com; England: StatsDirect, 2024).

Allocation concealment will be ensured through the use of opaque, sealed and numbered envelopes. The data regarding intervention assignments will be stored in a sealed envelope in a secure location within the administrative part of the department. An independent person will open the next consecutively numbered envelope and provide the allocation information to the study physician.

Since this is an open-label trial, both the participants and the study team will be aware of the treatment allocation on randomization. In the event of any medical issues, the assigned treatment information will already be accessible to the study physicians and principal researcher, eliminating the need for code-breaking procedures.

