### Statistical analysis

2.19

Descriptive statistics will be used to summarize baseline characteristics. For continuous variables, comparisons between groups will be made using the Student's *t*-test, Mann–Whitney *U*-test or Wilcoxon signed rank test, depending on whether or not the variables are normally distributed. The appropriate statistical test will be employed to compare percentages, either the χ^2^ test or Fisher's exact test.

For continuous outcomes, the differences in means or medians (depending on the distribution of data), and for dichotomous outcomes, the relative risk (RR) and number needed to treat (NNT), all accompanied by a 95% CI, will be calculated. The difference between study groups will be considered statistically significant if the *p*-value is less than 0.05, if the 95% CI for RR does not include 1.0, or if the 95% CI for mean difference does not include 0. All statistical tests will be two-tailed and performed at the 5% level of significance.

An intention-to-treat (ITT) analysis including all randomised participants, regardless of protocol adherence or withdrawal, will be applied. A per-protocol analysis that includes all participants who finish the study according to the protocol will also be performed.

The number of missing data with reasons will be reported for each study arm, and compared qualitatively between groups, if feasible. Multiple imputation methods for missing data will be applied to address missing data, as recommended (34).

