### Monitoring

2.20

The study will be carried out in accordance with the protocol, as it will be registered. No changes in the study protocol are expected to be made after the study starts. However, in case of any unexpected circumstances requiring alterations of the protocol, changes will be immediately applied to the protocol registry site at https://www.clinicaltrials.gov, and, if relevant enough, reported to the Bioethics committee of each participating institution. An independent Data and Safety Monitoring Board (DSMB) will be created before the start of the study. The DSMB will review data after recruitment from 25%, 50% and 75% of participants to assess the study progress (including rate of recruitment, completeness of data and their appropriate collection) and all the adverse events. The number of recruited patients will be monitored and kept up to date; appropriate changes (i.e., training of the recruiting physicians, study leaflets, addition of new recruitment centres) will be applied to the study procedure and protocol if the pace of recruitment is not high enough (or not sufficient) to finish the study within the established time of 4 years.

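### The abstract gives 84 as the number of children allocated, but section 2.9 makes 84 the number who complete and 94 the number recruited

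*Protocol article*

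**What the plan says.** The Methods paragraph of the abstract gives one sample-size figure and attaches it to allocation: "A total of 84 children with IgE-mediated HEA will be allocated in 1:1 ratio".

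Section 2.9 (Sample size justification) gives two figures. For entry, "a total of 94 children (47 per group) will be recruited to allow for an anticipated 10% dropout rate". For the end of the trial, it describes this as "ensuring that at least 84 participants (42 per group) complete the trial". The 84 is taken from a comparable baked-milk trial with 42 children per arm. It does not come from a power formula, since "A formal sample size calculation based on statistical power was not feasible".

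Two other places bear on how the figures relate. Section 2.16 (Sequence generation and allocation concealment) says "Children will be randomised to either the intervention or control group immediately after enrolment". Section 2.20 (Monitoring) fixes the timing of the board's reviews only as percentages: "The DSMB will review data after recruitment from 25%, 50% and 75% of participants".

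**The concern.** The same figure, 84, is the number allocated in one place and the number completing in another. Both statements can hold only if no child drops out, or if about ten children are recruited but never randomised. Section 2.9 excludes the first by allowing for 10% dropout. The second does not fit either. Randomisation follows enrolment directly, and section 2.9 states the loss per group (47 down to 42), whereas a child belongs to a group only once allocated.

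The number randomised sets the length of the allocation list, the point at which recruitment ends, the size of the intention-to-treat set in section 2.19, and the base for the percentage reviews in section 2.20. If the abstract's figure were followed, the trial would finish with fewer completers than section 2.9 says it will have.

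**Working it through.** **Inputs**
- Number allocated according to the abstract: 84, in a 1:1 ratio.
- Number recruited according to section 2.9: 94, that is 47 per group.
- Dropout according to section 2.9: 10%.
- Target completers according to section 2.9: at least 84, that is 42 per group.
- Link between recruited and allocated, from section 2.16: randomisation immediately after enrolment, so the two counts are equal.

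**Step 1. Reproduce the plan's own figure.** Number to recruit = completers / (1 − dropout), rounded up.
- Total: 84 / 0.90 = 93.3, rounded up to 94.
- Per group: 42 / 0.90 = 46.7, rounded up to 47, and 2 × 47 = 94.

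Section 2.9 reproduces exactly.

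**Step 2. Expected completers under each figure.** Expected completers = number randomised × (1 − dropout).

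| Randomised | Expected completers | Per arm | Against the target of 84 |
|---|---|---|---|
| 94 (section 2.9) | 94 × 0.90 = 84.6 | 42.3 | met |
| 84 (abstract) | 84 × 0.90 = 75.6 | 37.8 | 84 − 75.6 = 8.4 short |

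In whole children, 84 randomised gives about 76 completers, about 38 per arm, which is 8 to 9 short.

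**Step 3. Could 84 allocated still give 84 completers?** Only with no dropout at all. If each child drops out independently with probability 0.10, the chance of that is 0.90^84, about 0.0001. With 94 randomised, the binomial chance that at least 84 complete is about 0.66. So 94 meets the target in expectation and does not guarantee it.

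**Step 4. Base for the safety board's reviews.** 25%, 50% and 75% of 84 are 21, 42 and 63 children. The same percentages of 94 are 23.5, 47 and 70.5, so about 24, 47 and 71.

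**The case against.** The strongest reply is that this is a slip in the abstract and not a flaw in the design. Section 2.9 is the only sample-size section. It is explicit and correct, and nothing in the body uses 84 as a recruitment or randomisation target. The abstract also departs from the body elsewhere: it gives a 4-week break where section 2.5 has 6-week intervals, and two departments of one hospital where section 2.3 also lists a centre in Lodz. That pattern suggests an abstract that was not updated. This reply stands, and it limits the weight of the point. It does not remove the point, because the abstract is current text, its verb concerns allocation, and condensing a protocol explains an omission but not a conflicting number.

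A reader might infer three stronger things that the document does not support.

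- **That the trial loses power it had promised.** Section 2.9 states no power and no effect size, so there is no target to fall short of. The effect of the mismatch would depend wholly on the rates assumed. At the 80% versus 69% that the Introduction cites from an earlier randomised trial, chi-square power (two-sided 5%, exact binomial enumeration) is 23.0%, 21.4% and 19.8% at 47, 42 and 38 per arm, a change of under two points per step.
- **That two figures leave room to stop at 84 or go on to 94 once open-label results are seen.** No section provides for a stop that depends on outcomes, and the registry entry and allocation list are not shown. This is speculation.
- **That error control suffers through the shifted review points.** The reviews in section 2.20 cover progress, data completeness and adverse events. No efficacy stopping rule is stated.

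**Conclusion.** The inconsistency is real. The abstract gives the completer target as the number randomised, and only 94 agrees with the plan's own 10% dropout and 84 completers. If 84 were followed, the expected shortfall would be 8.4 completers, leaving about 38 per arm where section 2.9 has 42.

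The consequence is limited. Section 2.9 is internally correct and already holds the right figure. The main analysis includes all randomised participants, with multiple imputation for missing data, so the mismatch changes the size of that set and the completer count but not the validity of the test.

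The conclusion assumes that the 10% is taken at face value, that it applies after randomisation, and that enrolment and randomisation coincide as section 2.16 describes.

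**What to change.** Replace the abstract's sentence with wording such as: A total of 94 children (47 per arm) will be allocated in a 1:1 ratio; at least 84 are expected to complete, allowing for 10% dropout.

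Use 94 as the single randomisation target throughout. Confirm that the registry entry and the allocation list carry it, and take it as the base for the 25%, 50% and 75% reviews (about 24, 47 and 71 children).

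The cost is one sentence and a check. No children are added beyond those section 2.9 already plans to recruit, and no analysis changes.

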**Discussion:**

This rigorously designed RCT will provide evidence on the efficacy and safety of the 4-EL in children with IgE-mediated HEA. The findings will inform guideline development groups and further confirmatory trials.

**Trial Registration Number:**

NCT07040111, date of registration: 27 June 2025.

## Introduction

1

Hen's egg allergy (HEA) is one of the most common food allergies affecting the pediatric population, with an incidence of HEA of less than 1.2% in children under 2 years of age (1, 2). The standard of care for HEA is an elimination diet excluding hen's egg proteins. However, this approach, especially when followed long-term, presents several challenges, including delayed introduction of complementary foods, malnutrition, impaired growth, feeding difficulties and even social exclusion (3, 4).

Available evidence suggests that spontaneous resolution of HEA occurs in the majority of affected children over time. In the *EuroPrevall* study, 49% of children with HEA (*n* = 24/49) achieved tolerance to hen's egg proteins one year after diagnosis (1). Additionally, in the Australian *HealthNuts* cohort study, HEA resolved in 89% of participants (*n* = 287/323) by the age of 6 years (5). Nonetheless, a gradual reintroduction of heated egg using the egg ladder (EL) approach may accelerate the time to tolerance acquisition (6).

The egg ladder involves the gradual introduction of egg, beginning with less allergenic, extensively heated forms in small amounts, and progressing to lightly-cooked egg in regular, age-appropriate portions (7). The rationale for using the EL to assess tolerance acquisition is based on the lower allergenicity of baked compared to its unheated form. This reduction in allergenicity is attributed to the degradation of conformational IgE-binding epitopes caused by high-heat exposure (e.g., baking in the oven at 180°C for 30 min), as well as the “matrix effect” of the wheat-based batter – both shown to reduce IgE antibody binding to egg white proteins, thereby attenuating their allergenicity (8–10).

Leonard et al. demonstrated that the regular dietary inclusion of baked egg (e.g., a muffin or waffle containing 3.3 g of hen's egg proteins) reduced the time to tolerance induction to 50 months, compared to 78 months in children adhering to a strict egg avoidance diet (11). A 2025 systematic review summarized that in most studies, baked egg is safe and well-tolerated, with overall tolerance rates among children with HEA ranging from 70% to 97% (8, 9, 12). Furthermore, a 2024 systematic review and meta-analysis of 8 studies reported that 69% of children with HEA achieved tolerance to raw egg using the EL (95% CI: 0.5–0.85; *n* = 193) (8).

Allergology societies in different countries have proposed varying versions of the EL. However, discrepancies exist in both the number of steps included (ranging from 3 to 9 stages) and in the recommended intervals for progressing between each stage (ranging from 1 to 9 months) (12–17). Only one randomized controlled trial (RCT) has assessed the effect of a short-term EL protocol (18 months with 3–6 months break in periods) compared to a long-term protocol (30 months with a 9 months break in period) on hen's egg tolerance acquisition (12). This trial demonstrated a shorter time to achieve tolerance to unheated hen's egg (24 vs. 30 months) and a higher proportion of children attaining tolerance to raw egg (80% vs. 69%) in the short-term arm compared to control group (*n* = 78).

Currently, there are no standardized protocols for the assessment of tolerance acquisition using the EL approach. Furthermore, scientific evidence supporting the efficacy and safety of the EL in children with HEA remains limited.

## Methods and analysis

2

The study design followed established reporting standards, including the 2025 CONSORT Consolidated extension (Consolidated Standards of Reporting Trials) (18) and the SPIRIT 2025 (Standard Protocol Items: Recommendations for Interventional Trials) guidelines (19). In addition, the design incorporated the COMFA core outcome set for IgE-mediated food allergy research (20).

### Study objective and hypothesis

2.1

The primary aim of this study is to evaluate and compare the efficacy and safety of a 4-step egg ladder (4-EL) and a 5-step egg ladder (5-EL) in children diagnosed with IgE-mediated hen's egg protein allergy.

We hypothesize that the 4-EL, with 6-week intervals, will be sufficient for assessing tolerance to hen's egg proteins in children with IgE-mediated allergy and will result in a greater proportion of children achieving tolerance to raw egg white, confirmed by OFC, compared to the 5-EL, with the same timeframe. This corresponds to an 18-week tolerance acquisition period in the 4-EL group vs. 24 weeks in the 5-EL group.

There is some evidence suggesting that the introduction of baked egg in high-risk children (e.g., those with a history of anaphylaxis) may be both safe and effective (21). However, it remains unclear whether the initial tested dose of baked hen's egg protein in such cases should be lower than, or the same as, that recommended for the general pediatric HEA population.

Therefore, we decided to compare two ladder protocols: the 4-EL, beginning with a muffin containing 1.5 g of hen's egg proteins, and the 5-EL, in which the first two steps consist of muffins containing 0.75 g and 1.5 g of egg proteins, respectively. This approach allows for a reduced allergen load at initial exposure and a longer cumulative exposure to baked hen's egg proteins. Such a strategy may be more appropriate for specific subgroups of patients, particularly those considered to be at higher risk (21).

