### Intervention

2.5

All OFCs will be conducted in accordance with the PRACTical ALLergy (PRACTALL) guidelines (7).

Participants with IgE-mediated HEA will be randomly assigned to one of two groups: the intervention group (4-EL) or the control group (5-EL), with both protocols conducted over 6-week intervals (Table 2 and Supplementary Table S1).

**Table 2 T2:** Comparison of the 4-step (intervention) and 5-step (control) Egg ladder protocols in children with hen's Egg allergy.

Tested product (temperature, heating duration)	The amount of tested product	The amount of whole hen's egg proteins per portion [g]	The amount of hen's egg proteins per 100 g [g]	4- Step Egg Ladder (intervention group)	5- Step Egg Ladder (control group)
MUFFIN 0.75 Temp. 180°C (oven) Heating duration: 30 min (or until center is dry)	1 muffin (approx. 50 g)	0.75	1.5	–	STEP 1
6 weeks of regular dietary exposure to the tolerated quantity of the previously assessed forms					
MUFFIN 1.5 Temp. 180°C (oven) Heating duration: 30 min (or until center is dry)	1 muffin (approx. 50 g)	1.5	3	STEP 1	STEP 2
6 weeks of regular dietary exposure to the tolerated quantity of the previously assessed forms					
PANCAKE Temp. medium heat – approx. 180–190°C (frypan) Heating duration: 2–3 min both sides (until a golden-brown color is achieved)	1 pancake (approx. 84 g)	2.0	2.4	STEP 2	STEP 3
6 weeks of regular dietary exposure to the tolerated quantity of the previously assessed forms					
HARD- BOILED EGG Temp. approx. 100°C; should be added to the water once it reaches a rolling boil Heating duration: 10–12 min	1–3 years: 0.5–1 egg 4–5 years: 1 egg (approx. 50 g)	3.0 per 0.5 egg^a^ 6.0 per egg^a^	12.0	STEP 3	STEP 4
6 weeks of regular dietary exposure to the tolerated quantity of the previously assessed forms					
Almost raw egg: SOFT-BOILED EGG Temp. approx. 100°C; should be added to the water once it reaches a rolling boil Heating duration: 5 min	1–3 years: 0.5–1 egg 4–5 years: 1 egg approx. 50 g)	3.0 per 0.5 egg^a^ 6.0 per egg^a^	12.0	STEP 4	STEP 5
				Duration: 18 weeks	Duration: 24 weeks

a Amounts of hen's egg protein were estimated based on the average content in a medium egg (50 g).

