The 4-EL protocol [muffin (1.5 g hen's egg proteins), pancake, hard-boiled egg, and soft-boiled egg] and the 5-EL protocol (beginning with a muffin containing 0.75 g of hen's egg proteins, followed by 1.5 g, and then the remaining steps of the 4-EL) are both based on modifications of previously published egg ladders used in clinical practice (13, 15).

Instead of using raw egg as the final step, we chose to assess tolerance to soft-boiled egg, which is considered almost raw. This decision is justified mainly by practical considerations to increase parents and child's acceptability, and to prioritize the reintroduction of foods that are more likely to be regularly consumed in everyday diets.

At each step of the ladder, a single food product was selected and applied consistently across both study arms. The quantity of hen's egg proteins at each stage was determined based on recommendations from the PRACTALL consensus report (7) and the BSACI guidelines (15).

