#### Primary outcome

2.11.1

The primary outcome is the percentage of children who acquire tolerance to soft-boiled hen's egg (almost raw hen's egg proteins), as determined by a negative OFC at the final step of the EL. Soft-boiled egg will be administered at the end of the observation period (18 or 24 weeks, depending on the assigned study arm).

The challenge dose will consist of 0.5–1 egg for children aged 1–3 years and 1 egg for those aged 4–5 years, corresponding to a maximum total of 6 g of hen's egg proteins. The outcome will be reported as a difference between two study arms.

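### The superiority hypothesis and the abstract's primary outcome name raw egg, but the deciding challenge is soft-boiled egg, so a raw-egg conclusion would be unsupported

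*Protocol article*

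**What the plan says.** The food that defines success is named in two ways.

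- Section 2.1 (hypothesis): the 4-step ladder "will result in a greater proportion of children achieving tolerance to raw egg white, confirmed by OFC", compared with the 5-step ladder.
- Abstract, Methods: the primary outcome is tolerance to non-heated egg protein, "defined as non-allergic reaction to raw hen's egg (0.5–1 egg, depending on the age of the patient) during the last OFC".
- Section 2.11.1 (primary outcome) begins "The primary outcome is the percentage of children who acquire tolerance to soft-boiled" egg, adds in brackets that this is almost raw, and requires a negative challenge at the last step.
- Table 2: the last step in both arms is soft-boiled egg, put into boiling water at about 100°C for 5 minutes and given as whole egg.
- Section 2.5 states the substitution openly: "Instead of using raw egg as the final step, we chose to assess tolerance to soft-boiled egg". The reasons given are mainly practical: acceptability to families, and a preference for foods that children ordinarily eat.

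The interval between steps is also stated in two ways. The abstract has a "4-week break period between subsequent steps". Section 2.5 describes the trial "with both protocols conducted over 6-week intervals", and sections 2.1, 2.5.2, 2.6 and 2.7 and Table 2 also give 6 weeks. Abstract and Methods agree on 18 weeks for the 4-step arm and 24 weeks for the 5-step arm.

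**The concern.** The hypothesis says that a food challenge will confirm the result, but no planned challenge uses the food that it names. It also refers to egg white, whereas Table 2 doses whole egg. The mismatch is therefore not confined to the abstract; it sits in the Methods sentence that the superiority comparison is meant to address.

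The protocol's own rationale makes the difference matter. The Introduction explains the ladder by the lower allergenicity of heated egg, and section 2.6 orders the steps from more to less processed forms. On that logic an egg boiled for 5 minutes is not non-heated, and passing it does not by itself show tolerance of raw egg.

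The stake is the claim made at the end. The abstract and the Discussion say that the findings will inform guideline groups. A result reported in the abstract's terms would tell those groups that children tolerate raw egg when that was never tested.

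**Working it through.** **Endpoint food.** No arithmetic is needed to establish the mismatch; the places can be set side by side.

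1. Food in the hypothesis (2.1): raw egg white.
2. Food in the abstract's primary outcome: raw, non-heated egg, half to one egg by age.
3. Food at the last step of both ladders (Table 2): whole soft-boiled egg, half to one egg at 1–3 years and one egg at 4–5 years.
4. Food in the Methods primary outcome (2.11.1): soft-boiled egg, in the same portions.
5. Foods at the other steps (Table 2): muffin, pancake and hard-boiled egg, all heated. Section 2.14 allows another form of a food in case of feeding difficulties but requires the heating settings to be kept, so it does not bring in raw egg.

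Items 3 and 4 agree. Items 1 and 2 match no challenge in the trial.

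What would be needed to read a soft-boiled result as a raw-egg result? Let p be the proportion in an arm who pass the soft-boiled challenge, and q the fraction of those who would also pass a raw-egg challenge. Assume that a child who tolerates raw egg also tolerates soft-boiled egg. Then

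raw-egg tolerance = p × q, with q between 0 and 1.

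The documents give no value for q, so p is only an upper bound on raw-egg tolerance in each arm. The ratio between arms on raw egg is (p4 × q4) / (p5 × q5), which equals the soft-boiled ratio p4 / p5 only if q4 = q5. The trial measures p4 and p5. It measures neither q.

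**Interval.** Inputs: 4 or 5 steps, each opened by a challenge (section 2.6); the break between steps; the stated 18 and 24 weeks.

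Weeks to the last challenge = (number of steps − 1) × interval.

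- With the Methods' 6 weeks: 3 × 6 = 18 and 4 × 6 = 24. This reproduces the stated figures exactly.
- With the abstract's 4 weeks: 3 × 4 = 12 and 4 × 4 = 16, short by 6 and 8 weeks.
- 4 weeks after every step, including the last: 4 × 4 = 16 and 5 × 4 = 20.
- 4 weeks between steps plus the 6-week follow-up of section 2.8: 12 + 6 = 18 and 16 + 6 = 22.
- Interval implied by the stated durations: 18 / 3 = 24 / 4 = 6 weeks.

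None of these ways of counting 4-week breaks gives both stated durations.

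**The case against.** The strongest reply is that the operative endpoint is clear. Table 2 and section 2.11.1 agree with each other, section 2.5 discloses the replacement of raw egg and gives reasons, and soft-boiled egg is called almost raw wherever it is defined. On this view the abstract and section 2.1 carry loose wording, and nothing in procedure, sample or analysis is wrong. Most of this stands. It does not rescue the hypothesis or the abstract. The reasons given for the substitution are practical and offer no evidence that passing one food implies passing the other.

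Three stronger readings are tempting, and the documents do not support them.

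- A reader might infer that the trial cannot answer its question. The primary aim in section 2.1 is to compare the efficacy and safety of the two ladders. Both end in the same challenge with the same portions, and section 2.11.1 reports the difference between arms. That comparison can be made.
- A reader might infer that two definitions leave room to choose the more favourable result. No raw-egg result can exist, because no raw-egg challenge is planned. The risk is mislabelling, not selection.
- A reader might infer that results will be set against the raw-egg rates in the Introduction (69% in a meta-analysis; 80% versus 69% in an earlier trial). No section plans this. Those figures are background, and the statistical section describes comparisons between groups only.

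On the interval, the reply is that every Methods statement says 6 weeks and the abstract's own durations agree. That is correct: it is a clerical slip in the abstract and has no bearing on the endpoint.

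**Conclusion.** The endpoint contradiction holds and should be corrected, because it concerns what the primary result means. The superiority hypothesis as worded is not tested by any challenge in the protocol, and a conclusion about raw or non-heated egg would be unsupported. The comparison of the two ladders on soft-boiled egg is unaffected. This is a fault of wording with consequences for the conclusion; it is not a failure of design.

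The size of any gap between soft-boiled and raw-egg tolerance cannot be derived from the documents. The conclusion does not depend on that size. It rests on the protocol's own premise that heating lowers allergenicity, and on the absence of any stated equivalence between the two foods. The registry record was not available, so nothing is said about its wording.

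The interval discrepancy is real and minor: 12 and 16 weeks under the abstract's break, against the stated 18 and 24.

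**What to change.** Reconcile the abstract and section 2.1 with section 2.5, Table 2 and section 2.11.1, so that one challenge food defines the hypothesis, the primary outcome and the conclusion. If the Table 2 challenge stands, word all three as tolerance to soft-boiled egg as prepared there, remove the terms raw egg, raw egg white and non-heated from the hypothesis and the primary outcome, and confine the conclusion to the food tested. Which food the trial ought to use is a clinical matter and is not judged here.

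Separately, reconcile the abstract's 4-week break with the 6-week intervals in the Methods and with the 18 and 24 weeks that both give.

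The cost is a text correction to the abstract and section 2.1. If the Table 2 challenge is kept, no procedure, sample size or analysis changes, and the only downside is a narrower claim.
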